**Results:**

A total of 960 patients from 20 urological centers will be randomized to receive either suction mini-PCNL or standard PCNL. Intention-to-treat analysis will be performed. For SFR, non-inferiority will be concluded if the lower bound of the 95% confidence interval for the absolute risk difference exceeds − 10%. For operative time, non-inferiority will be concluded if the lower bound of the 95% confidence interval for the mean difference exceeds − 10 min. For all other analyses, a two-sided p-value of < 0.05 will be regarded as statistically significant. Subgroup analyses will be performed to explore potential effect modification by stone location and stone density.

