### Surgical protocol

A standardized operative protocol will be established to ensure uniformity across all centers. Periodic protocol monitoring visits will be conducted to ensure its adherence at all participating centers.

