#### PCNL procedures

Ultrasound-guided puncture to the target calyx will be performed using an 18-gauge coaxial needle. Retrograde pyelogram via the ureteral catheter will confirm the puncture position, followed by guidewire insertion. Tract dilatation over guidewire will be accomplished using fascial dilators.

For standard PCNL, 24Fr sheath will be inserted, and 20Fr nephroscope (Richard Wolf, Germany) will be used. Renal stones will be fragmented and aspirated using an ultrasonic-lithotripter (LithoClast Master, EMS or ShockPluse-SE, Olympus).

For suction mini-PCNL, 18Fr suction sheath (Wellead, China) will be inserted, and 12Fr mini-nephroscope will be used. Renal stones will be fragmented by pneumatic lithotriptor or Ho: YAG laser (1.0–2.0 J ×20–30 Hz), and stone fragments will be aspirated out via the suction sheath.

Upon conclusion of the procedure, fluoroscopy will be utilized to detect any residual stones. If present, further attempts, including the possible creation of additional tracts, will be made to remove all residual fragments. Double-J stent and/or nephrostomy tube will be inserted at the discretion of the operating surgeon. Tubeless PCNL may be feasible if there is no significant residual stone, bleeding, collecting system perforation, or ureteral obstruction.

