#### Statistical analysis

Intention-to-treat analysis will be performed. All enrolled participants with complete data will be included in the analysis. Statistical analyses will be conducted using Statistical Package for Social Sciences (SPSS) 22.0 or above and R software version 4.3.1 or above (R Foundation for Statistical Computing). Continuous data will be presented as median (IQR) and analyzed using Student’s t test or Mann-Whitney U test, as appropriate. Categorical data will be expressed as n (%) and compared using the χ2 test or Fisher’s exact test, as appropriate.

Pre-specified sensitivity analyses will be performed to assess the robustness of the primary findings under alternative, clinically plausible noninferiority margins. These sensitivity analyses will include SFR noninferiority margins of − 5% and operative time noninferiority margins of − 5 and − 10 min, respectively. These analyses will be exploratory in nature and are intended to evaluate the consistency of conclusions across different noninferiority thresholds, rather than to redefine the primary hypotheses or decision criteria. Subgroup analyses will be performed to explore potential effect modification by stone location, stone density and lithotripsy energy modality. Logistic regression and linear regression models including a treatment-by-subgroup interaction term will be used to evaluate the interaction effect on SFR and operative time, respectively.

This trial includes two co-primary endpoints: postoperative SFR and operative time. To control the overall type I error rate, a joint noninferiority testing strategy based on the intersection–union principle will be applied. Noninferiority of suction mini-PCNL will be concluded only if both co-primary endpoints independently satisfy their respective noninferiority criteria. Specifically, for SFR, non-inferiority is defined if the lower bound of the 95% confidence interval for the absolute risk difference exceeds − 10%. For operative time, non-inferiority is defined if the lower bound of the 95% confidence interval for the mean difference exceeds − 10 min. For all other analyses, a two-sided p-value of < 0.05 will be regarded as statistically significant.

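### The planned treatment-by-lithotripsy-modality interaction cannot be estimated when the protocol is followed, because each modality belongs to one arm only

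*Protocol article*

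**What the plan says.** The Statistical analysis section names three subgroup factors: "Subgroup analyses will be performed to explore potential effect modification by stone location, stone density and lithotripsy energy modality". It then fixes the model: "Logistic regression and linear regression models including a treatment-by-subgroup interaction term will be used to evaluate the interaction effect on SFR and operative time, respectively".

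The PCNL procedures section ties the energy source to the arm. For standard PCNL: "Renal stones will be fragmented and aspirated using an ultrasonic-lithotripter (LithoClast Master, EMS or ShockPluse-SE, Olympus". For suction mini-PCNL: "Renal stones will be fragmented by pneumatic lithotriptor or Ho: YAG laser (1.0–2.0 J ×20–30 Hz". No modality, as labelled there, appears under both techniques.

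The Surgical protocol section says: "A standardized operative protocol will be established to ensure uniformity across all centers". It adds that adherence will be monitored by visits to the centres. The Discussion lists varying energy modalities as a possible source of heterogeneity, but does not say that any modality is shared between the arms.

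**The concern.** A treatment-by-factor interaction asks whether the difference between arms changes across the levels of the factor. That needs at least two levels in which both arms are represented. Here no level contains both arms, so there is no within-modality treatment effect to compare. The plan names an analysis that the trial's own intervention rules make impossible.

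Modality also differs in kind from the other two factors. Stone location and density are properties of the stone before surgery, and density is measured on the preoperative CT. Modality is part of the delivered intervention, applied after randomisation, and Table 1 does not list it among the recruitment variables. Even with overlap between arms it would be a poor choice of effect modifier.

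At stake is the meaning of one exploratory result on each co-primary endpoint. The contrast of the three modalities that remains, beyond the arm difference itself, is laser versus pneumatic within the suction mini-PCNL arm. That contrast is not randomised and is not effect modification.

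**Working it through.** The article gives no figure for this analysis, so there is none to reproduce. The check is whether the stated model can be estimated from the combinations that the protocol allows.

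**Inputs.** Modality by arm comes from PCNL procedures, the interaction model from Statistical analysis, and 480 patients per group from Sample size. The pneumatic/laser split within the suction arm is not stated, so two splits were assumed: 240/240 and 120/360.

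**Coding.** A = 1 for suction mini-PCNL, P = 1 for pneumatic, L = 1 for laser, with ultrasonic as reference. The linear predictor contains intercept, A, P, L, A×P and A×L. It is the same for the logistic and the linear model.

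| Combination allowed | Intercept | A | P | L | A×P | A×L |
|---|---|---|---|---|---|---|
| Standard, ultrasonic | 1 | 0 | 0 | 0 | 0 | 0 |
| Suction mini, pneumatic | 1 | 1 | 1 | 0 | 1 | 0 |
| Suction mini, laser | 1 | 1 | 0 | 1 | 0 | 1 |

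Three of the 2 × 3 = 6 cells are empty: standard/pneumatic, standard/laser and suction mini/ultrasonic.

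**Rank.** In every row A×P = P, A×L = L and A = P + L. Six columns minus three exact dependencies leaves rank 3. The main-effects columns (intercept, A, P, L) also have rank 3.

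- Interaction df = rank(full) − rank(main effects) = 3 − 3 = 0.
- Treatment df given modality = rank(intercept, A, P, L) − rank(intercept, P, L) = 3 − 3 = 0. Even a modality-adjusted treatment effect is not identified.

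A numerical check with 480 patients per arm gave these values for both assumed splits.

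**Other codings of modality.**

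- Ultrasonic versus other: the factor is the arm itself (other = A), so the interaction adds nothing: 2 − 2 = 0 df.
- Laser versus not laser: three occupied cells, and A×L = L, so 3 − 3 = 0 df.
- Pneumatic versus not pneumatic: the same, with A×P = P, so 3 − 3 = 0 df.

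**Hypothetical departures from the protocol (three modalities kept apart).**

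| Scenario | Rank, full | Rank, main effects | Interaction df |
|---|---|---|---|
| As the protocol states | 3 | 3 | 0 |
| 10 pneumatic cases in the standard arm | 4 | 4 | 0 |
| 10 pneumatic cases in the standard arm and 10 ultrasonic cases in the suction arm | 5 | 4 | 1 |
| All three modalities in both arms | 6 | 4 | 2 |

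One crossover is not enough. Two modalities must each occur in both arms before 1 df exists.

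**The case against.** The strongest reply has four parts.

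*It is exploratory.* This stands. The noninferiority conclusion rests only on the two confidence-interval criteria, and neither uses this model. It limits the weight of the point but does not make the analysis computable.

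*Coding and detail belong in the full protocol or analysis plan.* The article does leave the coding of modality open. But it states both the factor and the interaction model, and no coding of the three modalities gives the interaction a degree of freedom while the procedures section stands. This is a conflict between two stated passages, not an omitted detail.

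*Devices will vary in practice, and intention-to-treat keeps such patients.* Off-protocol use could fill empty cells, so the result holds under adherence, not in every conceivable dataset. Any estimate would then rest on a few protocol departures. If modality were collapsed to pneumatic versus other, a single crossover would give 4 occupied cells and 4 − 3 = 1 df, but the other category would be mainly ultrasonic in one arm and laser in the other, which is not a common level.

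*A related question can be answered.* Laser-suction and pneumatic-suction cases could each be set against the whole standard arm. That is feasible, but it is not an interaction, the two suction subsets are not randomised, and the article does not describe it. It does show that rewording can preserve the interest in modality.

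A reader might also infer more than the article supports. It does not say who selects pneumatic or laser: the wording on surgeon's discretion concerns antibiotics and the stent or tube, and centre equipment could equally decide. Silent software failure followed by a false report of effect modification is a prediction; a program may instead flag the aliased terms, and the test may simply be abandoned. The abstract names only two factors ("Subgroup analyses will be performed to explore potential effect modification by stone location and stone density"), but abstracts condense, so this is not evidence that the main text is wrong.

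**Conclusion.** The point holds in a narrow form. As written, the treatment-by-modality interaction for SFR and operative time has 0 df (rank 3 of 6 columns), because modality is nested within arm. Enlarging the trial would not help while the device rules are followed.

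This rests on two assumptions: the device labels in PCNL procedures are taken at face value, and they are adhered to. The unknown pneumatic/laser split does not matter.

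A reader might go further and take this as a threat to the trial's main conclusion. The documents do not support that. The sample size, the joint test of the co-primary endpoints and the subgroup analyses by stone location and stone density are all untouched. It is a correction worth making to one of three exploratory subgroup factors.

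**What to change.** Reconcile PCNL procedures with Statistical analysis. Under the device assignment as it stands, remove lithotripsy energy modality from the interaction analyses and keep stone location and stone density.

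If modality is of interest, add a sentence saying that SFR and operative time will be described by laser versus pneumatic within the suction mini-PCNL arm, as a non-randomised comparison and not as effect modification. Whether and how to adjust that description is the trial team's choice; nothing in the article dictates it.

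If the authors do intend some modalities to be used in both arms, the procedures section should say so. Which devices are used is a clinical matter on which this point takes no position.

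The cost is about one line of analysis text. No sample size, primary test or surgical step changes, and no information is lost, because the planned interaction cannot be computed under the protocol. The change should be made before unblinding so that it cannot look data-driven.

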### Sample size

The reported SFRs following suction mini-PCNL and standard PCNL for 2–4 cm renal stones are 83% and 86% respectively [3, 10, 13, 15]. We hypothesize that the SFR following suction mini-PCNL is noninferior to standard PCNL. The noninferiority margin is prespecified at -10%, based on clinical consensus and prior randomized controlled trial [15]. Assuming a one-sided α of 0.025, a power of 80%, and a noninferiority margin of -10% [15], the minimum required sample size per group is calculated to be 419. Considering an anticipated withdrawal and loss to follow-up rates of approximately 10%, this is adjusted to 480 participants per group, resulting in a total sample size of 960.

The reported operative times for mini-PCNL and standard PCNL in the management of 2–4 cm kidney stones are comparable [15]. Since suction mini-PCNL is faster than mini-PCNL [13], we conservatively assume that there is no difference in operative time between suction mini-PCNL and standard PCNL. The reported standard deviation is approximately 15 min [13, 16]. Our hypothesis is that the operative time for suction mini-PCNL is noninferior to that of standard PCNL. Assuming a one-sided α of 0.025, a power of 80%, and a noninferiority margin of -10 min, the minimum required sample size per group is calculated to be 43, which is smaller than the sample size determined based on SFR.

Thus, the final total sample size is set at 960.

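### The operative-time non-inferiority rule tests the wrong confidence limit: suction mini-PCNL passes however much slower it is, and fails if it is much faster

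*Protocol article*

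**What the plan says.** The two co-primary endpoints are immediate SFR and operative time. Under the intersection-union strategy in Statistical analysis, both must pass before non-inferiority is claimed.

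- **SFR rule** (Statistical analysis): "for SFR, non-inferiority is defined if the lower bound of the 95% confidence interval for the absolute risk difference exceeds" −10%.
- **Operative-time rule** (Statistical analysis, the next sentence): "For operative time, non-inferiority is defined if the lower bound of the 95% confidence interval for the mean difference exceeds" −10 min.
- **Abstract, Results:** "For operative time, non-inferiority will be concluded if the lower bound of the 95% confidence interval for the mean difference exceeds" −10 min.
- **Sample size:** "Assuming a one-sided α of 0.025, a power of 80%, and a noninferiority margin of -10 min". The other inputs are "The reported standard deviation is approximately 15 min" and "we conservatively assume that there is no difference in operative time between suction mini-PCNL and standard PCNL". The result is stated as "the minimum required sample size per group is calculated to be 43, which is smaller than the sample size determined based on SFR".
- **Sensitivity margins for time** (Statistical analysis): −5 and −10 min.

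No section states the order of subtraction for either endpoint.

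**The concern.** A lower-limit rule with a negative margin guards against the new treatment being worse only when low values of the difference are bad. That is true of SFR taken as suction mini-PCNL minus standard PCNL. It is not true of operative time taken in the same order, where a slower new technique gives a positive difference. The article treats longer surgery as the harm: the Introduction names it as a likely drawback of the smaller tract, and the Discussion links it to more complications and a lower SFR.

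An intersection-union test controls type I error only if each component test is valid. If the time criterion cannot fail a slower technique, the joint conclusion rests on SFR alone, and the planned claim of non-inferiority in operative time has no support. The rule can also sink the trial for the opposite reason: a suction technique that saves well over 10 min would fail the time criterion, and so the joint test.

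**Working it through.** **Step 1. Which order of subtraction does the article support?**

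The SFR sample size settles it for SFR. The inputs from Sample size are 83% (suction mini-PCNL), 86% (standard PCNL), margin 10 points, one-sided α 0.025 and power 80%.

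- Variance term: 0.83 × 0.17 + 0.86 × 0.14 = 0.1411 + 0.1204 = 0.2615.
- (1.96 + 0.8416)² = 7.849.
- Suction minus standard = −3 points, so the distance to the margin is 10 − 3 = 7 points: n = 0.2615 × 7.849 / 0.07² = 418.9, rounded up to **419**, the stated figure.
- With the sign reversed (a 3-point advantage) the distance is 13 points: n = 0.2615 × 7.849 / 0.13² = 121.4, rounded up to 122.

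So the SFR difference is suction mini-PCNL minus standard PCNL. The time rule follows it directly, with parallel wording and the same sign, and no section announces a reversal.

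**Step 2. The operative-time sample size cannot settle the order.** The assumed true difference is 0, so the calculation is the same in either direction.

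- n = 2 × 7.849 × 15² / 10² = 35.3, so 36 per group (37 with the t distribution).
- The stated 43 is not reproduced. It appears if 0.025 is treated as two-sided: z = 2.2414, and 2 × (2.2414 + 0.8416)² × 15² / 10² = 42.8, so 43.

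**Step 3. How often does each rule pass?** Let d be the true difference, suction minus standard. Inputs are SD 15 min and 480 × 0.9 = 432 evaluable per arm.

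- SE = 15 × √(2/432) = 1.0206 min; CI half-width = 1.96 × 1.0206 = 2.00 min.
- Rule as written (lower limit > −10): P = Φ((d + 10)/SE − 1.96). It passes whenever the observed difference exceeds about −8.0 min.
- Correct rule (upper limit < +10): P = Φ((10 − d)/SE − 1.96).

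| True d (min) | Rule as written | Upper limit < +10 |
|---|---|---|
| −12 (faster) | <0.0001 | 1.000 |
| −10 | 0.025 | 1.000 |
| −8 | 0.50 | 1.000 |
| −5 | 0.998 | 1.000 |
| 0 | 1.000 | 1.000 |
| +5 | 1.000 | 0.998 |
| +10 (slower) | 1.000 | 0.025 |
| +20 | 1.000 | 0.000 |
| +30 | 1.000 | 0.000 |

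Two entries worked through:

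- d = +10, as written: 20/1.0206 − 1.96 = 17.6, so P ≈ 1. Correct rule: 0 − 1.96, so P = 0.025.
- d = −12, as written: −2/1.0206 − 1.96 = −3.92, so P < 0.0001.

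The pattern is the same with 419 or 480 per arm.

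**The case against.** The strongest reply is that the article never gives the order of subtraction for time. If time is taken as standard minus suction (minutes saved), negative values mean the new technique is worse. The lower-limit rule is then valid and identical to an upper limit below +10 min in the other order. Orienting every endpoint so that negative means worse is a coherent convention, and the negative time margin is used consistently throughout. The protective intent is plain, and the full protocol or SAP may define the contrast.

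Part of this stands. The article does not exclude that reading in words, and the figures in the table hold only for suction minus standard. But the reply needs an unstated reversal between two adjacent rules of the same form, and the SFR figures fix the order for the first of them. Nor is this a detail left to another document: the article states the pass/fail rule itself, twice. Even on the favourable reading, the verdict on a co-primary endpoint turns on a sign convention that is never given, and the two conventions give opposite answers for a clearly slower or much faster technique.

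It is also fair to say that 43 against 36 or 37 per group is a separate and minor matter. It errs on the large side, does not affect the total of 960, and adds no weight to this point.

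**Conclusion.** The concern holds. On the only order of subtraction the article supports, the operative-time criterion checks the wrong limit. At the inferiority boundary of 10 min slower, its type I error is about 100% instead of 2.5%, and a technique truly 12 min faster would fail more than 99.9% of the time. The time endpoint therefore gives no protection against slower surgery, and the joint claim reduces to the SFR test.

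The figures assume an SD of 15 min, 432 evaluable patients per arm, a normal approximation, and differences taken as suction minus standard. The result is not sensitive to the number evaluable. It would change only if time were explicitly defined as standard minus suction. This must be corrected before analysis.

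**What to change.** - **Abstract (Results) and Statistical analysis:** state that all differences are suction mini-PCNL minus standard PCNL, and that operative time is non-inferior if the upper limit of the two-sided 95% CI for the mean difference is below +10 min. Leave the SFR rule as it is.
- **Sample size:** give the operative-time margin as +10 min. While editing, correct 43 to 36 per group (37 with the t distribution), or state the inputs that give 43.
- **Sensitivity analyses for time:** replace the listed −5 and −10 min with +5 min. The 10-min margin is already the primary criterion, so listing it again adds nothing.

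Defining time explicitly as standard minus suction and keeping the lower limit would also be valid. However, it would leave the two co-primary endpoints with opposite orders and is easier to misread.

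The cost is a wording correction in three sections, with no change to data collection, visits or the total of 960. It should be made before any unblinded comparison of operative times.

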## Discussion

Endourology has witnessed monumental technological advances, particularly with the introduction of suction in lithotripsy interventions and miniaturization of surgical equipment in the recent years.

Several studies have compared the clinical outcomes of mini-PCNL with those of standard PCNL, but reported inconsistent findings. The general consensus is that mini-PCNL holds the advantage of less invasiveness over standard PCNL, accounting for less blood loss and shorter hospital stay. However, the postoperative SFR of mini-PCNL is similar to standard PCNL for moderate-sized kidney stones [3, 10, 15]. The relatively longer operative time in mini-PCNL remains a topic of concern [10]. Since complication rates generally increase with prolonged operative time while SFR decreases, improving lithotripsy efficiency in mini-PCNL is an urgent priority.

The suction-assisted technique in lithotripsy has gained popularity in both PCNL and retrograde intrarenal surgery (RIRS) [19, 20]. Suction technique in mini-PCNL enables active aspiration of stone fragments, dust, blood clots, thereby maintaining excellent visualization at a low intrarenal pressure level, preventing stone migration, and facilitating the stone removal process, while mitigating the limitations of conventional mini-PCNL [13].

Beyond enhancing stone removal efficiency in mini-PCNL, suction can improve SFR, shorten operative time and reduce the need for auxiliary procedures [21, 22].

Concerning postoperative complications, existing literature has demonstrated that the overall complication rate in the suction mini-PCNL group is significantly lower than that of the conventional mini-PCNL group, particularly for postoperative fever, septic shock and blood loss [21, 22]. The well controlled IRP and shorter operative time by suction may account for the reduction in complication rates compared to conventional mini-PCNL [12].

To date, there is no large sample size randomized controlled trial (RCT) comparing suction mini-PCNL with standard PCNL. Given the promising outcomes of suction application in mini-PCNL, our study aims to compare suction mini-PCNL with standard PCNL for the treatment of 2–4 cm renal stones. The co-primary outcomes will assess the noninferiority of suction mini-PCNL versus standard PCNL in terms of SFR and operative time.

Complication profiles are also critical for evaluating PCNL; thus, secondary outcomes include postoperative complications, postoperative pain, length of hospital stay and QoL, on top of final SFR at 1 month. Despite the robust trial design, there are potential limitations, such as possible heterogeneity in terms of patient selection and treatment protocols (e.g. different lasers, energy modalities utilized, surgeon’s experience).

As an academic organization dedicated to urolithiasis prevention and treatment, the International Alliance of Urolithiasis (IAU) is committed to conducting this well-designed RCT to generate robust evidence to guide clinical practice. If suction mini-PCNL is proven non-inferior to standard PCNL in terms of SFR and operative time, this study will establish suction mini-PCNL as a feasible treatment option to standard PCNL with comparable efficacy and safety, particularly in patients at higher bleeding risks or seeking rapid recovery.

To the best of our knowledge, the present study is the largest RCT to compare the efficacy and safety of suction mini-PCNL with standard PCNL for 2–4 cm kidney stones. Our findings will advance renal stone treatment, optimize clinical strategies, and enhance the healthcare services quality, ultimately benefiting patients.

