### Patients population

The inclusion criteria are as follow: (1) Adults aged 18–70 years; (2) American Society of Anesthesiology (ASA) score of 1–2; (3) Kidney stones measuring 2–4 cm in diameter on non-contrast computer tomography; (4) Ability to provide written informed consent and adhere to trial requirements.

The exclusion criteria are as follow: (1) Anatomy abnormalities, such as urinary diversion, horseshoe kidney, transplanted kidney, or ureteropelvic junction obstruction; (2) Untreated acute urinary tract infection (UTI); (3) Patients on anticoagulant/antithrombotic therapy, or with uncorrected coagulopathies; (4) Patients who decline trial enrolment or cannot adhere to trial requirements.

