#### Outcome measures

##### Primary outcomes

The co-primary outcomes are the immediate postoperative stone-free rate (SFR) and operative time. Immediate postoperative SFR is defined as the absence of residual stone or fragments < 2 mm on low-dose NCCT scan within 72 h after operation. Operative time is defined as the time from percutaneous puncture to completion of double-J or nephrostomy tube placement.

Secondary outcomes are as follows: Final SFR: defined as no residual stone or fragments <2 mm on NCCT (2 mm slice) at 1 month post intervention.Pain VAS score.Length of hospital stay: calculated from the day of surgery to the day of discharge, rounded to the nearest whole day.Postoperative complications up to 1 month post-intervention, evaluated using the Clavien-Dindo classification.QoL will be assessed preoperatively and at 1 month postoperatively by the WisQoL questionnaire.

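### The Discussion lets success on stone-free rate and operative time stand as proof of comparable safety, singling out patients at higher bleeding risk, although safety is no part of the success criterion and the main haemostatic-risk groups are excluded

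*Protocol article*

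**What the plan says.** The Discussion states in advance how a positive result will be read. The condition is: "If suction mini-PCNL is proven non-inferior to standard PCNL in terms of SFR and operative time, this study will establish". What is then established is suction mini-PCNL "as a feasible treatment option to standard PCNL with comparable efficacy and safety, particularly in patients at higher bleeding risks"; the sentence goes on to add patients who want a quick recovery.

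The other relevant parts of the protocol article are narrower:

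- **Statistical analysis, decision rule:** "Noninferiority of suction mini-PCNL will be concluded only if both co-primary endpoints independently satisfy their respective noninferiority criteria". Those endpoints are immediate SFR (margin −10 percentage points) and operative time (margin −10 min).
- **Statistical analysis, everything else:** "For all other analyses, a two-sided p-value of < 0.05 will be regarded as statistically significant".
- **Outcome measures:** safety appears among the secondary outcomes as "Postoperative complications up to 1 month post-intervention, evaluated using the Clavien-Dindo classification". No margin is given for it.
- **Sample size:** calculations are given for SFR and operative time only.
- **Patients population:** the exclusions include "Patients on anticoagulant/antithrombotic therapy, or with uncorrected coagulopathies", and entry requires an "American Society of Anesthesiology (ASA) score of 1–2".
- **Statistical analysis, subgroups:** stone location, stone density and lithotripsy energy modality, with interaction models for SFR and operative time.

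**The concern.** The sentence has safety in its conclusion but not in its condition. Read literally, the trial could meet both co-primary criteria, observe more complications in the suction arm, and still satisfy the stated condition for calling the two procedures comparable in safety.

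The sentence then gives special weight to patients at higher bleeding risk. The groups most readily identified by that description, those on anticoagulant or antithrombotic drugs and those with uncorrected coagulopathy, cannot be enrolled. No planned analysis isolates any other patients who might fit it.

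At stake is what the trial will be taken to show. The Discussion says that the trial is meant to guide practice. A reader could carry a safety conclusion to patients at bleeding risk when it was not tested and was largely not studied in them.

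**Working it through.** **1. The plan's own size calculation, to see what it rests on.** Inputs (Sample size section): SFR 86% standard, 83% suction mini, margin 10 points, one-sided α 0.025, power 80%.

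n per group = [0.86×0.14 + 0.83×0.17] × (1.960 + 0.842)² / (0.10 − 0.03)² = 0.2615 × 7.849 / 0.0049 = 418.9, so 419. This matches the stated 419. The plan raises it to 480 for about 10% loss. No complication rate or safety margin enters, and the second calculation in that section concerns operative time.

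**2. Condition against conclusion.**

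| Element | Success condition | Stated conclusion |
|---|---|---|
| SFR | Yes, with margin | Yes (efficacy) |
| Operative time | Yes, with margin | Yes (efficacy) |
| Complications, bleeding | No criterion | Yes (safety) |
| Patients at higher bleeding risk | Main haemostatic groups excluded; no subgroup | Singled out |

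The last two rows do not match.

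**3. How precisely the trial could describe safety (illustration only).** The documents give no complication rate, so rates of 5% to 20% are assumed. Evaluable patients per arm: 480 × 0.90 = 432.

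Half-width of the 95% confidence interval for the risk difference at equal rates p: 1.96 × √[2p(1 − p)/432].

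| Assumed rate | Half-width (points) |
|---|---|
| 5% | 2.9 |
| 10% | 4.0 |
| 15% | 4.8 |
| 20% | 5.3 |

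Chance that a two-sided 5% test misses a true rise from p₁ to p₂: 1 − Φ{[(p₂ − p₁) − 1.96·SE₀]/SE₁}, with SE₀ = √[2p̄(1 − p̄)/432], p̄ the mean of the two rates, and SE₁ = √{[p₁(1 − p₁) + p₂(1 − p₂)]/432}.

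| True rise | SE₀ | SE₁ | Non-significant |
|---|---|---|---|
| 5% to 8% | 0.01677 | 0.01674 | 57% |
| 10% to 14% | 0.02211 | 0.02207 | 56% |
| 15% to 20% | 0.02585 | 0.02580 | 51% |

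For the first row: (0.03 − 1.96×0.01677)/0.01674 = −0.172; Φ = 0.432; 1 − 0.432 = 0.568.

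So neither success on the co-primary endpoints nor a non-significant complication test would by itself show comparable safety.

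**The case against.** The strongest reply is that this is one closing sentence in a Discussion and not an analysis rule. The Study objectives speak of surgical efficiency, the abstract's conclusion speaks only of non-inferiority, and the decision rule is confined to the two co-primary endpoints. That is right, and it limits the point: no test, sample size or dataset is at fault. It does not rescue the sentence, which says what the study will establish and on what condition.

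Safety is also not neglected. Complications to 1 month are a graded secondary outcome, bleeding has its own line in Table 1, and the Discussion calls complication profiles critical. This stands: the defect is in the inference, not in data collection. How secondary outcomes are tabulated may properly be left to a fuller document.

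Three stronger readings are tempting, and the documents do not support them:

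- **That the plan will treat a non-significant complication test as evidence of comparability.** No text says so. The Statistical analysis section sets only a significance threshold, and the Discussion sentence does not depend on the complication p-value at all.
- **That every patient at higher bleeding risk is excluded.** The exclusion covers anticoagulant or antithrombotic therapy and uncorrected coagulopathy. Patients with corrected coagulopathy, or with bleeding risk from the stone or the access, may still enter. The ASA limit is a general fitness criterion that the documents do not tie to bleeding.
- **That the percentages above measure a fault in the design.** They rest on assumed rates, and limited power for a secondary outcome is ordinary.

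Finally, the bleeding-risk phrase may be meant to name who would prefer the option, given the reduced bleeding that the article reports for mini-PCNL. That is a reasonable motive for the trial. But the complication evidence that the Discussion cites for suction compares it with conventional mini-PCNL, and the article says no large randomized comparison with standard PCNL exists. Earlier evidence is not something that this study will itself establish.

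**Conclusion.** The point holds in a limited form. The Discussion draws a conclusion on safety from a success condition that contains no safety criterion, and it stresses patients whose main haemostatic-risk groups are excluded and for whom no subgroup is planned. The decision rule needs no change; the conclusion attached to it does.

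This rests on comparing the sections of the article and on no assumed figure. The calculations serve only to show that safety would be estimated with moderate precision, about ±2.9 to ±5.3 points at assumed rates of 5% to 20% with 432 evaluable per arm. Rises of 3 to 5 points at the rates examined would escape a significance test slightly more often than not.

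**What to change.** Reword the Discussion sentence in three respects:

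1. State that meeting both criteria supports non-inferiority of suction mini-PCNL on SFR and operative time only, in the population enrolled.
2. Describe safety separately, from the risk differences for complications and bleeding with 95% confidence intervals. Make no claim of comparable safety that follows from success on the co-primary endpoints or from a non-significant test.
3. Delete the phrase on higher bleeding risk, or qualify it by saying that patients on anticoagulant or antithrombotic therapy or with uncorrected coagulopathy were not studied and that no bleeding-risk subgroup was planned.

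The cost is wording only: design, sample size, data collection and decision rule stay as they are. The downside is a narrower stated claim.
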